## **8.4 Investigator’s Site File**

At each study site, the Investigator is responsible for maintaining all records to enable the conduct of the study to be fully documented. Essential documents as required by GCP guidelines and regulations (e.g., copies of

the protocol, study approval letters, all original informed consent forms, site copies of all CRFs, drug dispensing and accountability logs, correspondence pertaining to the study, etc.) should be filed accurately and kept by the Investigator for the maximum period of time required by local regulations.

The Investigator is responsible for maintaining a confidential patient identification code list, which provides the unique link between named source records and CRF data for the Sponsor. The Investigator must arrange for the retention of this confidential list for the maximum period of time required by local regulations.

No study document should be destroyed without prior written agreement between the Investigator and the Sponsor. Should the Investigator elect to assign the study documents to another party, or move them to another location, the Sponsor must be notified in writing.

## **8.5 Provision of Additional Information**

On request, the site investigators will supply the Sponsor or designate, such as the monitors with additional data relating to the study, or copies of relevant source records, ensuring that the patient's confidentiality is maintained. This is particularly important when CRFs are illegible or when errors in data transcription are encountered. In case of particular issues or governmental queries, it is also necessary to have access to the complete study records, provided that the patient's confidentiality is protected in accordance with applicable regulations.

## **8.6 Independent Data Safety Monitoring Committee**

An IDSMC will be established by the Sponsor. The IDSMC will be composed of recognized experts in the field of statistics, perioperative medicine, and hematology who are not actively recruiting patients.

A written study-specific charter will define in detail the composition, responsibilities, and procedures of the IDSMC.

## 9 STATISTICAL METHODS AND SAMPLE SIZE

The statistical analysis will be delegated under an agreement of transfer of responsibilities to an external statistician. Details on planned descriptive and exploratory analyses will be provided in a separate Statistical Analysis Plan (SAP).

### 9.1 Determination of Sample Size

This pilot study will include 120 randomized patients, which, accounting for randomized but untreated patients and patients who withdraw in both arms, is expected to provide at least 100 evaluable patients, with 50 in each arm. This population is expected to be clinically sufficient to allow selection of an appropriate endpoint for the confirmative Phase 3 study and to determine feasibility. No statistical sample size estimation has been involved.

### 9.2 Statistical Analysis

For the statistical analysis of the efficacy parameters the following analysis populations will be considered:

The statistical analyses will be performed on the intention to treat (ITT) population, which will include all randomized and treated patients who consent to the study. Randomized patients who did not undergo cardiac surgery or received no IMP will be excluded from the analysis. It is anticipated that <20% of patients will fall into these categories. In the event that a patient receives treatment that is not in concordance with the randomization schedule, the treatment group will be defined according to the randomization (rather than the actual treatment received).

The per-protocol (PP) population: This analysis population will consist of all patients in the ITT population, excluding patients with important protocol deviations that may affect the statistical analysis. The following patients will be excluded by default:

- Patients who receive an IMP different to the IMP assigned by randomization
- Patients who receive less than 80% of the planned dose
- Patients who significantly violate inclusion/exclusion criteria

A final decision about the classification of protocol deviations and their consequences regarding assignment of patients to analysis populations will be made during the data review meeting prior to the final analyses. Decisions and outcome will be approved by the Principal Investigator (Sponsor) in consultation with the funder (Octapharma).

The ITT analysis population is considered the primary population for analysis of the efficacy objectives.

Descriptive statistics with 95% confidence intervals will be used to describe the data. Simple tests of comparison will be used to compare outcomes between the two groups. The summary tables and exploratory inferences will be chosen according to the scaling level of the measurements, e.g. frequency tables and Chi-square tests for categorical responses, sampling statistics and F-tests for continuous data.

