### Revision history

| SAP Version | Version date | Reason(s) for change                                                                                                                                                                                                                                                                                                                                                                                                                                                                                                                               |
|-------------|--------------|----------------------------------------------------------------------------------------------------------------------------------------------------------------------------------------------------------------------------------------------------------------------------------------------------------------------------------------------------------------------------------------------------------------------------------------------------------------------------------------------------------------------------------------------------|
| 1.0         | 2020-04-30   | Not applicable. First version.                                                                                                                                                                                                                                                                                                                                                                                                                                                                                                                     |
| 2.0         | 2020-09-21   | 
Changes required by discussions during Blinded Data Review Meeting:
 
 
• Add exploratory analysis to assess the dependence of treatment response on compliance (section 3.6),
 
• Add exploratory analysis to assess endpoints in different time frames
 
• Add another secondary endpoint applying a conservative response definition.
 
• Clarify that ‘other’ medical history will only be listed and only prespecified conditions will be summarized (section 4.4).
 
 |

|                                  |                        |                    |                     |
|----------------------------------|------------------------|--------------------|---------------------|

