## 2 GENERAL INFORMATION

### 2.1 Background details

All study data will be transferred to a SAS database (version 9.4 or later) for statistical analysis purposes. Data will be imported from an Electronic Data Capture System (OPVerdi) via validated SAS programs. If applicable, external data will also be transferred to SAS for presentation of these data in the statistical analyses.

The SAP will be finalized before any unblinded analysis after agreement with the Sponsor.

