### 2.3 Individual protocol deviations

No specific protocol deviations will be considered as this is a non-interventional, pragmatic study.

A detailed review of all documented and derived deviations from protocol will be part of the Data Review Meeting (DMR) before database lock. During this DRM the impact of protocol deviations on the analysis will be assessed and the conclusions documented.

A complete listing of protocol deviations (documented as well as derived ones) and the judgment for assessment of subject disposition will be signed before clinical database lock. A description of protocol violations that led to exclusion from any analysis sets will be included in the table part of the Clinical Study Report (CSR).

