## 3 ANALYSIS POPULATIONS

Due to the emergency nature of the condition being studied the trial will include only patients who are incapable of providing informed consent at the time the therapy is needed and in whom delays in obtaining surrogate consent can be severely detrimental to their well-being. Thus, this study qualifies for alteration to consent requirement before randomization. Therefore delayed consent from patients or surrogate decision maker (SDM) where appropriate will be sought after surgery.

As a rule, only data from enrolled patients with informed consent will be analyzed.

Data from randomized and treated patients who refused to give consent will be excluded from any analysis.

To ensure that the safety reporting is complete, all hemostatic therapy and severe or life-threatening serious adverse event data will be collected in cases where consent for remaining in the study cannot be obtained.

|                           |                 |             |              |
|---------------------------|-----------------|-------------|--------------|
| Statistical Analysis Plan | Version 2.0     |             | Page 9 of 19 |
| Sponsor                   | [name] | Protocol No | FARES        |

Hence, the disposition of patients will be displayed according to the following analysis populations:

- All Patients Enrolled (APE) population
- Failed Consent Patients (FCP) population
- Safety (SAF) population
- Intention-To-Treat (ITT) population
- Per-Protocol (PP) population

Membership of subjects will be decided upon in a DRM with the Sponsor before database lock. The proper flags for analysis sets exclusion (e.g., exclusion from PP set), will be included in the analysis datasets. The protocol deviation list should be finalized before database lock.

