### 3.5 Per-Protocol (PP) Population

The Per-Protocol (PP) Population will include all patients of the IIT population, excluding patients with important protocol deviations that may affect the statistical analysis. The following patients will be excluded by default:

- Patients who receive an IMP different to the IMP assigned by randomization
- Patients who receive less than 80% of the planned dose
- Patients who significantly violate inclusion/exclusion criteria

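### The test product's manufacturer is consulted on deviation classification and analysis-set assignment, the per-protocol exclusions are open-ended, and SAP 2.3 contradicts SAP 3.5

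*Combined protocol and SAP*

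**What the plan says.** **Who decides.** Protocol 9.2 says that the final decision on deviations and on "assignment of patients to analysis populations will be made during the data review meeting prior to the final analyses". It continues: "Decisions and outcome will be approved by the Principal Investigator (Sponsor) in consultation with the funder (Octapharma". SAP 3 says: "Membership of subjects will be decided upon in a DRM with the Sponsor before database lock". Protocol 1.4 describes the funder's grant as unrestricted, and also has the funder supporting data management and statistical services.

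**What is excluded from the PP set.** Protocol 9.2 and SAP 3.5 share a general clause that removes patients whose deviations are judged important, and three default exclusions:
- "Patients who receive an IMP different to the IMP assigned by randomization"
- "Patients who receive less than 80% of the planned dose"
- patients who breach the eligibility criteria to a significant degree. Neither document defines important or significant.

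**What SAP 2.3 says.** "No specific protocol deviations will be considered as this is a non-interventional, pragmatic study". The same section then requires a detailed review of deviations, a listing signed before database lock, and a description in the study report of violations that led to exclusion.

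**Blinding of the meeting.** The word appears only in the SAP revision history: "Changes required by discussions during Blinded Data Review Meeting". SAP 2.1 adds: "The SAP will be finalized before any unblinded analysis after agreement with the Sponsor".

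**The concern.** A company with a commercial interest in the test product has a stated role in deciding which patients count. That role covers judgements for which the plan sets no criterion. Excluding a few non-responders from one arm as important deviations would improve that arm's PP result, so the people who make these calls should have neither an interest in the result nor sight of arm and outcome.

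The documents do not secure the second condition. Under protocol 7.2.2 all products released and transfused are collected from the blood bank. The arms are dosed in different units (IU and U), so an unmasked dosing listing would show the arm. A second IMP dose, a platelet transfusion or another haemostatic agent within the assessment window is also a failure on treatment response (P1), so the same listing would show part of the outcome. No section says what is masked at the meeting or who derives the flags.

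SAP 2.3 makes this worse. Read literally, its first sentence cancels the default exclusions that SAP 3.5 lists, so a programmer has two conflicting rules for the PP set.

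**Working it through.** The point is procedural and the plan gives no figure to reproduce. The check sets the sections side by side and adds two small calculations.

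**1. Where discretion lies.**

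| Set | Criteria | Judgement needed? |
|---|---|---|
| ITT (SAP 3.4) | consent, at least one treatment, cardiac surgery; grouped as randomised | No |
| Safety (SAP 3.3) | consent, at least one treatment; grouped as treated | No |
| PP, default 1 (SAP 3.5) | product received differs from product assigned | No |
| PP, default 2 | under 80% of planned dose | No |
| PP, default 3 | significant eligibility breach | Yes, undefined |
| PP, general clause | important deviations | Yes, undefined |

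SAP 3 sends every set to the meeting, but only the PP set has criteria that leave room for choice. Protocol 9.2 and SAP 4.6 make ITT the primary efficacy population. SAP 4.6 repeats the primary endpoints on the PP set.

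**2. Can the two factual PP rules be applied without showing the product?** The first needs only a match/mismatch flag. The second needs only received dose divided by planned dose. Planned doses (protocol 5.1.1) are 1500 or 2000 IU of PCC and 3 or 4 U of FP. Assume that a shortfall comes in whole steps of 500 IU or 1 U:
- Above 60 kg, one step short: PCC 1500/2000 = 75%; FP 3/4 = 75%.
- At or below 60 kg, one step short: PCC 1000/1500 = 66.7%; FP 2/3 = 66.7%.

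The percentages agree between arms and fall below 80% in every case. A percent-of-plan flag therefore applies the rule without revealing the arm. The plan simply does not provide for such a flag.

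**3. SAP 2.3 against SAP 3.5.** SAP 1.2 calls the study a randomised, active-control Phase 2 pilot, so it is not non-interventional. SAP 2.3 says no specific deviations are considered; SAP 3.5 specifies three. Both cannot stand.

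**4. How far could a few PP exclusions move the result?** The 50 per arm is the protocol 9.1 target. **The response counts and the number excluded are assumptions; the documents give none.** The test is the two-sided Fisher exact test named in SAP 4.6. FP keeps all 50 patients, and only PCC non-responders are removed.

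| FP | PCC before (ITT) | p | Removed | PCC after (PP only) | Difference after | p |
|---|---|---|---|---|---|---|
| 30/50 | 38/50 | 0.133 | 3 | 38/47 | 80.9% − 60.0% = 20.9 points | 0.029 |
| 35/50 | 42/50 | 0.153 | 2 | 42/48 | 87.5% − 70.0% = 17.5 points | 0.048 |
| 30/50 | 36/50 | 0.291 | 3 | 36/47 | 76.6% − 60.0% = 16.6 points | 0.087 |
| 32/50 | 38/50 | 0.275 | 3 | 38/47 | 80.9% − 64.0% = 16.9 points | 0.074 |
| 30/50 | 30/50 | 1.000 | 3 | 30/47 | 63.8% − 60.0% = 3.8 points | 0.835 |

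Over assumed PCC response rates of 50% to 84%, removing one to five non-responders raises the PCC rate by 1.0 to 9.3 points. Whether p crosses 0.05 depends on the starting counts. Columns one to three, which are the ITT result, do not change.

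**The case against.** The strongest reply is that the documents point to a proper process. The meeting is called blinded, the SAP is to be final before any unblinded analysis, and the deviation listing is signed before lock. Approval rests with the sponsor-investigator; the funder is only consulted. Protocol 9 delegates the analysis to an external statistician, and SAP 3 names only the Sponsor at the meeting. The tests are exploratory, the sample size was not statistically derived, and no decision is tied to p < 0.05.

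Most of this stands, and it rules out several stronger readings that a reader might infer:

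- *The meeting must see the product to apply the rules.* It need not: a match flag and a percent of plan are enough.
- *Patients are excluded with arm and outcome visible.* No section says that either is shown. SAP Appendix 1 puts the treatment arm on all subject listings, but it describes final output. SAP version 2.0 followed the meeting and added a compliance analysis, further time frames and a conservative response definition. This suggests that response and compliance were discussed, not that results by arm were seen.
- *ITT and safety results are exposed too.* Their criteria are factual.
- *SAP 2.3 leaves exclusions wholly undefined.* SAP 3.5 supplies defaults, and the rest of 2.3 requires review, sign-off and reporting.

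Three things remain. The funder's consultation is written into the protocol, with no limit on what it may see. The undefined PP criteria are the ones on which consultation could matter. The first sentence of SAP 2.3 is an error on any reading.

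**Conclusion.** The point holds as a minor one. The plan gives the manufacturer of the test product a stated consultative role in classifying deviations and assigning patients to sets. It leaves two PP exclusions to undefined judgement, and it does not prevent arm-revealing data from being seen when those judgements are made. SAP 2.3 separately contradicts SAP 3.5 on a false description of the design.

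The effect is confined to the supportive PP analysis of the primary endpoints. On the assumed counts above, two or three one-sided exclusions could carry a PP comparison across 0.05 in some scenarios and not in others, with ITT untouched. The documents do not show that this happened or that the meeting was unblinded. The undescribed masking would be only missing detail by itself; the funder's role and the conflicting rule are what justify a change.

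**What to change.** 1. In protocol 9.2, delete the clause on consulting the funder. Alternatively, state that the funder takes no part in classification until the analysis sets are signed.
2. In SAP 2.3, delete the first sentence and refer to SAP 3.5.
3. In SAP 3.5, have the two factual PP flags (product match/mismatch, percent of planned dose) derived by program by someone independent of trial conduct. The biostatistician who prepares the allocation schedule, described in protocol 3.3.5 as not involved in conduct, would be suitable.
4. Make the remaining judgements on a listing without product, units or P1 outcome, and sign membership before those fields are available.

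Cost: protocol and SAP wording and one masked listing. The funder loses a consultation step. No patient, visit or treatment is affected.

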### 9.2.1 Safety Analysis Plan

The safety analysis population (SAF) will include all patients who received at least one dose of the IMP who consent to the study (if no randomization errors occur, this will be the same population as the ITT population). Safety outcomes will be analyzed by presenting point estimates and two-sided 95% CIs in addition to descriptive statistics.

To ensure that the safety reporting is complete, all hemostatic therapy and Grades 3 and 4 SAE (as per the FDA criteria: severe or life-threatening) data will be collected in cases where consent for remaining in the study cannot be obtained.

#### **Adverse events, including thromboembolic and other events of special interest**

AEs will be coded according to the latest Medical Dictionary for Regulatory Activities (MedDRA) version as specified in the Data Management Plan. The analysis will focus on treatment emergent adverse events (TEAEs), i.e., AEs that started or worsened after start of infusion with IMP.

All TEAEs, related TEAEs (i.e., AEs unlikely, probably or possibly related to the IMP), and serious TEAEs will be summarized and tabulated according to primary system organ class and preferred term. TEAEs leading to death and TEAEs resulting in withdrawal from the study will be tabulated using frequency tables if a reasonable number of events of this type are observed.

Analogous frequency tables for thromboembolic events (TEEs, identified using MedDRA SMQs), composite events, TRALI and TACO will be provided separately.

Patient listings will be provided for patients with SAEs, TEEs, AEs leading to withdrawal from the study, and AEs leading to death. Listings for non-treatment emergent adverse events, e.g. for patients enrolled but not randomized will be provided separately.

#### **Mortality**

The number of patients who died will be summarized. A possible difference between treatment groups will be estimated by a risk ratio with 95% CI. Kaplan-Meier estimates for the time to death distribution will be calculated and graphically presented if a sufficient number of cases have been registered.

#### **Routine laboratory data**

All laboratory values will be classified as normal or abnormal according to the laboratories' normal ranges and indicated as clinically significant or not clinically significant by the Investigator on specified ranges. The following approaches will be taken for each laboratory parameter for the statistical analysis:

- Quantitative data will be examined for trends using descriptive analysis (number of patients, number of missing values, mean, SD, median, quartiles, minimum, maximum) of actual values at each scheduled time point and changes from baseline to each scheduled time point. Mean concentration vs time profiles will be plotted for quantitative data
- Qualitative data based on reference ranges will be described according to the categories (i.e., low, normal, high)

- Shift tables illustrating changes with respect to the laboratories' normal ranges between baseline and a defined scheduled time point. Scatterplots between scheduled time points of lab values with normal ranges will be used for visual illustration.
- Number and frequency of patients with clinically significant laboratory values. A separate patient listing will be provided

### 9.2.2 Subgroup Analysis

Due to the exploratory character of this pilot study efficacy and selected safety results will further be investigated within subgroups.

This will be done to detect possible relationships that procedural or patient characteristics may have on the response parameters.

If the levels of subgroups (e.g. surgery types) are too numerous to form subgroups of sufficient size, the influence of the characteristic will be studied using model-based exploratory analyses (e.g. logistic regression, Analysis of Covariance, Proportional hazards regression).

Details on the subgroup and model-based inferences will be given in a Statistical Analysis Plan that will be finalized before the Data Review Meeting.

